#### Feasibility

Feasibility will be assessed in 2 ways: (1) passive retention of participants in the intervention and follow-up phases, indicated by ongoing electronic sensor syncing and (2) text message and its usefulness, acceptability, and preferences, assessed via questionnaire. To assess passive retention, we will monitor duration of the interval that the electronic sensor synced with its receiver (either a mobile phone app or cellular hub). In order to sync effectively, the Bluetooth-enabled sensor must be within range of a functioning (plugged in) cellular hub or an open mobile phone app with Bluetooth enabled. Thus, passive retention represents whether the receiver was capable of transmitting MDI actuations from the sensor during the intervention and follow-up phases of the study. Reasons for missing actuation data will be collected during the follow up calls and during individual calls for participants whose sensors fail to sync within the first 2 days of the intervention phase of the study.

Perceived usefulness, acceptability, and intervention preferences will be measured using a 14-item questionnaire developed de novo for this study and delivered to those who receive the intervention either at follow-up call 1 or 2 (See Figure 1). This survey focused primarily on usefulness and acceptability of the daily text messages, as our prior work in a similar population found electronic sensors to be generally acceptable [24] (see Multimedia Appendix 1).

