#### Limited Efficacy

Limited efficacy outcomes for this study will include (1) percent ICS adherence, as measured by electronic monitoring and (2) average change in parent-reported asthma control, assessed using the parent-reported portion of the child Asthma Control Test [25]. Inhaled controller medication use will be measured in both groups using electronic sensors (see description below) affixed atop of the MDI canister. ICS adherence will be calculated from the daily medication use data as the average percent adherence (observed actuations or prescribed actuations) for the intervention group versus the control group for the 30-day intervention phase. The average change in the parent-reported portion of the child Asthma Control Test score between enrollment and the 30-day follow-up call will be calculated for the intervention and control groups.

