### Intervention

#### Enrollment

Potential subjects will be screened through the daily census listings for the ED and general pediatrics inpatient units at CHOP, using the protocol inclusion and exclusion criteria. Parents of eligible participants will be approached for informed consent, screening, and enrollment prior to the patient’s discharge from the hospital. Child assent will be obtained from children ages 7 years and older, unless the child is judged to be incapable of assent. If subjects provide consent and enroll, they will complete the initial study visit prior to hospital or ED discharge. As part of enrollment, caregivers will complete an initial 30-minute survey on the Way to Health (WTH) platform (see below for description). Prior to survey completion, participants will be randomized into either the control or intervention group using a 1:1 randomization scheme, stratified by location (ED or inpatient). Each participant will be compensated US $20 through a reusable debit card following completion of each survey, for a total of US $60 for those completing the entire study.

Following the baseline survey, a study team member will attach an electronic sensor to the participant’s ICS inhaler. If the participants do not have a currently filled ICS prescription with them in the hospital room, they will be instructed on how to attach the sensor to the child’s inhaler when they get home. Participants whose sensors are not attached to the inhaler at discharge will be contacted by phone to achieve an initial sync. Participants who have mobile phones will download the Propeller mobile phone app for data transmission purposes, but the participants will not have access to any information from the app. Preferences for the text messages, which are delivered to the parents’ mobile phone via the Way to Health platform (time of day and preferred phone number), will be collected for all participants. Participants will be instructed to use the inhaler as directed by their physician and that they may begin to receive automated text message reminders regarding their child’s medication use.

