#### Intervention Phase

The randomized intervention begins the day of discharge from the hospital and lasts 30 days. During this time, the intervention group will receive daily automated text message reminders from the WTH platform at a time of their choosing. In addition to daily text message reminders for the intervention group, both the intervention and control groups will receive programmed text messages when they reach milestones in the study, such as survey or intervention completion. These text messages will also serve as prompts to contact study staff and complete their next survey. The research team will also program text messages reminding participants to continue syncing their electronic monitoring sensor with its receiver by turning on their Bluetooth, if they are using a mobile phone, or by making sure that their hub is plugged in, if not. A total of 3 syncing reminders will be sent over the course of the intervention. Study staff will send individualized text messages or call participants if the sensor fails to sync in the first 2 days of the intervention phase. Researchers will walk the participant through the syncing process and record any reasons for missing data.

At the end of the 30-day period, families will receive a text message instructing them to set up a follow-up call within the next few days. If the participants don’t call within 2-4 days, they will be contacted by the research team. The first follow-up call includes a 10-minute survey for all participants and the questionnaire assessing acceptability and preferences for participants in the intervention arm. After completing the surveys, participants will be asked to choose whether or not to receive text message reminders during the follow-up phase of the study. Automated text messages will be turned on or off for each individual through WTH. All participants will be asked whether they have run out of ICS medication and if they had any problems using the electronic sensor. Any problems that may lead to missing data will be recorded. The participant will then be reminded to transfer the electronic sensor to their new inhaler if or when the prescription is refilled.

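### The only described reminder to move the sensor to a refilled inhaler comes after the 30-day adherence window, so doses from an earlier refill can be scored as missed

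*Protocol article*

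**What the plan says.** **Outcome.** Limited Efficacy (Outcome Measures) defines the measure: "ICS adherence will be calculated from the daily medication use data as the average percent adherence (observed actuations or prescribed actuations". I read this as observed actuations divided by prescribed actuations. The contrast and its window are then given as "for the intervention group versus the control group for the 30-day intervention phase".

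**First attachment.** Under Enrollment, once the first survey is done, "a study team member will attach an electronic sensor to the participant’s ICS inhaler". Families with no filled inhaler in the room are handled differently: "they will be instructed on how to attach the sensor to the child’s inhaler when they get home". The section does not require the inhaler to be new or full.

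**Contacts during the 30 days.** Under Intervention Phase: "A total of 3 syncing reminders will be sent over the course of the intervention". Their stated content is Bluetooth and the hub. Staff text or call if the sensor fails to sync in the first 2 days. The Limitations section adds reminder calls shortly after discharge, aimed at filling the prescription and attaching the sensor.

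**Transfer at refill.** This appears once, within follow-up call 1: "The participant will then be reminded to transfer the electronic sensor to their new inhaler if or when the prescription is refilled". That call is arranged only once the window has ended, to take place some days later: "At the end of the 30-day period, families will receive a text message instructing them to set up a follow-up call within the next few". Staff make contact when no call has come after 2-4 days.

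**Retention.** Feasibility (Outcome Measures) explains the retention measure this way: "passive retention represents whether the receiver was capable of transmitting MDI actuations from the sensor".

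**The concern.** The sensor measures use of one canister, while the outcome is meant to measure the child's use of the medicine. The two part company when the child moves to another inhaler and the sensor does not. The plan leaves three routes to this before day 30:

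- a part-used inhaler is fitted at enrollment (every child must have been prescribed an ICS in the prior year, so this is possible);
- the canister holds fewer than 30 days of prescribed doses;
- the sensor is fitted to an older inhaler and the discharge prescription is filled later.

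A sensor left behind can still sync. Passive retention then looks complete, and restricting the analysis to synced days would not find the problem. Staff see when a sensor last synced but are blind to actuations until the end of the intervention interval (Propeller Health System), so they would not notice that puffs had stopped. Doses from the unsensored inhaler enter the ratio as doses not taken.

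At stake is the direction of error. Heavier users empty a canister sooner, so if the reminders work, more of the loss falls in the intervention arm and the observed difference shrinks. The Limitations section says that these differences will be used to judge trends for future efficacy testing, and a bias towards no difference would mislead that judgment.

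**Working it through.** The protocol states no figure to reproduce: it gives no canister size, puffs per day, effect size or standard deviation. The check is of the mechanism, with assumed inputs shown as ranges.

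**From the protocol.** Window of 30 days; cited adherence of 11-37% in urban minority populations and about 50% in childhood asthma generally (Introduction); 40 children randomized 1:1.

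**Assumed.** C = puffs left on the sensored canister at discharge; d = prescribed puffs per day; a = true adherence; no sensor transfer; canister used until empty.

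**Formulas.** Recorded adherence = min(a, C/(30d)). Run-out day = C/(a × d).

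**Cap, C/(30d).**

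| C | d = 2 | d = 4 | d = 8 |
|---|---|---|---|
| 30 | 50% | 25% | 12.5% |
| 60 | none | 50% | 25% |
| 90 | none | 75% | 37.5% |
| 120 | none | none | 50% |

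A canister holding at least 30 days of prescribed doses produces no cap inside the window.

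**Who is affected.** Take C = 60 and d = 4, so the cap is 60/120 = 50%. The loss is 0 points at a = 11%, 37% or 50%; 25 points at 75% (run-out on day 60/3 = 20); and 50 points at 100%. At 37% the canister lasts 60/1.48 = 40.5 days, beyond the window. With only 30 puffs left the cap is 25%: 37% is recorded as 25%, and 11% is unchanged.

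**Effect on the arm difference.** Adherence was simulated from beta distributions with SD 0.25 (assumed) and 400,000 draws per arm. Differences are in percentage points.

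| True means, control v intervention | True difference | 50% cap on everyone | 50% cap on a quarter |
|---|---|---|---|
| 24% v 37% | 13.0 | 10.7 | 12.5 |
| 37% v 50% | 12.9 | 8.0 | 11.7 |
| 37% v 70% | 33.0 | 14.5 | 28.4 |

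The last column can be checked by weighting: 0.75 × 33.0 + 0.25 × 14.5 = 28.4, and 0.75 × 12.9 + 0.25 × 8.0 = 11.7. With a 75% cap on everyone, 33.0 becomes 26.1 and 12.9 becomes 11.8.

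**Limit of the formula.** If a family switches while puffs remain on the old canister, the loss is whatever is taken after the switch, at any adherence level. The protocol gives nothing from which to size that case.

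**Trajectories.** The trajectory analysis uses both phases. At C = 120 and d = 4, a full adherer runs out on day 120/4 = 30. If the family refills before the call without moving the sensor, recorded use falls to zero while true use continues. That would look like the post-discharge decay the trajectory analysis is meant to describe.

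**The case against.** Most of the case on the other side is sound, and it narrows the point considerably.

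- **Earlier teaching is possible.** The sentence speaks of a reminder, which allows for earlier instruction, and a journal article need not reproduce the enrollment script. A reader might infer that families are told about transfer only after day 30. The text does not support that; it supports only that no earlier instruction is described.
- **Most sensors probably go on a new inhaler.** The Limitations section says that most families leave with a new prescription, links staff fitting to its being filled on site, and has other caregivers attach the sensor after filling it themselves. Part-used canisters are then likely a minority. The same passage does leave open that a family fitted on an older inhaler fills the new prescription inside the window.
- **Low adherence rarely reaches the cap.** At the cited 11-37%, few families would run out before day 30.
- **Some information is collected.** Call 1 asks everyone about run-out and sensor problems, and prescription changes are listed among the reasons for missing actuation data. But those reasons are recorded only if the caregiver describes them, and neither a refill date nor a sensor move is described as being collected.
- **Passive retention is not misdefined.** It claims only that data could be transmitted, not that every dose was captured.
- **This is a pilot.** Primary outcomes are feasibility, and the protocol disclaims power for adherence.

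What these points do not remove is the stated timing. The one described transfer reminder cannot protect the 30-day comparison, and no described check would reveal a sensor left behind.

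**Conclusion.** The point holds as a conditional measurement weakness of low severity. It depends on a child changing inhaler before day 30 and the sensor not being moved. For a canister used until empty, recorded adherence is then capped at C/(30d), the loss is confined to adherers above the cap, and a real arm difference is biased towards zero.

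Its size cannot be fixed from the protocol. With a 50% cap on a quarter of participants, 33.0 points appears as 28.4 and 12.9 as 11.7. These figures rest on the assumed share, cap and SD.

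A much larger distortion might be inferred. With 4 puffs per day and 60 left, 80% is recorded as 60/120 = 50% and 40% as 48/120 = 40%, so a true 40-point difference shows as 10. That would need the canisters in both arms to start with half a month of doses, nobody to move the sensor, and adherence far above the cited range in the intervention arm. The protocol does not support this as a typical case.

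The primary feasibility aim is unaffected. The exposure is in the 30-day adherence comparison and, for refills between about day 30 and the call, in the exploratory trajectories.

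**What to change.** 1. At enrollment, show every family how to transfer the sensor at refill, including those whose sensor is fitted by staff.
2. Add one sentence on transfer to the three syncing texts already planned for participants in both arms.
3. At call 1, next to the existing run-out question, record the date of any refill and whether the sensor was moved.
4. Treat days on an unsensored refill as not monitored, not as missed doses. Days with no medication on hand stay as doses not taken.

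The cost is a short demonstration at an existing visit, a sentence in existing messages and two call items. Treatment does not change, and both arms are handled alike. The small downside is that refill dates rest on caregiver recall.

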#### Follow-up Phase

The follow-up phase begins the day the first follow-up call is completed and continues until 60 days following the start of the randomized intervention. The follow-up phase lasts up to 30 days. Participants will be given 2 weeks following the end of the follow-up period to complete the second follow-up call.

At 60 days, medication adherence monitoring and optional text message reminders will cease and families will receive a message from the study team to set up a second follow-up call (the study completion call) within the next few days. If the participants don’t call within 2-4 days, the research team will contact them. The second follow-up call includes a 10-minute survey for all participants. Participants will be asked again whether they have run out of ICS medication or if they had any problems using the electronic sensor and responses will be recorded. Participants initially assigned to the control group who elected to receive text messages during the follow-up phase will also complete the acceptability and preferences questionnaire.

### Way to Health Platform

Way to Health (WTH) is a Web-based behavioral intervention toolbox, which automates many of the research functions necessary for conducting randomized controlled trials (waytohealth.org). For this study, the WTH platform will be customized to enroll participants, automate randomization and text message delivery, and complete and store survey data. For participants in the intervention arm, 7 rotating text messages will be programmed into WTH. Each text message will include a reminder to administer the ICS inhaler as well as an asthma-related tip or fact (Figure 3). Each family will be able to customize the time the text message reminders are sent based on caregiver preference.

The Way to Health Platform protects patient information by using a secured firewall accessible only to study research, analysis, and IT staff by use of a password.

**Figure 3 figure3:**
[figure not shown]
Examples of intervention text messages.

### Propeller Health System

We will use Propeller Health electronic monitoring sensors to monitor ICS medication use (propellerhealth.com). Propeller Health sensors record the date, time, and number of inhaler actuations. The Propeller Health sensors have been validated and used in previous studies [33,34].

Families with a mobile phone will use the sensor in conjunction with a research “control” version of Propeller Health’s mobile app, which receives the medication use data from the sensor through the mobile phone’s Bluetooth functionality. Unlike the full Propeller Health mobile app, which provides medication usage summaries, adherence, control status, air quality information, education and personalized trigger information to the participant, the research version provides only medication use and timing data to an encrypted server accessible to the research team alone. Families without a mobile phone will be provided an electronic monitoring device with a paired cellular hub. The hub transmits medication use data from the device to the encrypted server through cellular networks and must be plugged into an electrical outlet for transmission.

The communication between the electronic monitoring sensors and the Propeller Health server is referred to as syncing. Syncing transmits data on inhaler actuations, which refers to medication usage recorded by the sensor. One actuation translates to one single use or puff of the participant’s daily controller medication. The Propeller Health research app allows study staff to see when each participant’s electronic monitoring sensor last synced with the server. However, it does not display data on device actuations. Thus, study staff will know if a participant’s sensor is syncing, but will be blind to each participant’s medication usage data until the end of the intervention interval. The Propeller Health platform will not be used to store protected health information.

### Data Analysis

#### Feasibility

Response rate will be defined as number of participants who complete enrollment, out of the total number of eligible patients who we approach. Passive retention will be evaluated using the median number of days for which the sensor syncs with its mobile phone or hub. Qualitative reasons for missing actuation data (eg, logging out of the app, failing to plug in the hub, or prescription changes) will be recorded if described by the caregiver during follow up or syncing issue calls described above. We will use summary statistics (mean, interquartile range) to describe Likert-based usability, acceptability, and preferences question responses. Qualitative responses regarding what participants liked most about the study and what would make it better will be evaluated for the most common responses.

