### Participants – Inclusion and Exclusion Criteria

Participants will include 40 children aged 2 to 13 years and their parent or legal guardian. To be enrolled in the study, children and their parent or legal guardian must meet the following eligibility criteria: (1) they must be receiving care for asthma on the ED or inpatient asthma pathways; (2) they must have been prescribed a daily ICS or combined ICS or long-acting beta agonist (LABA) in the year prior to the current admission and the ICS prescribed on discharge must be an MDI compatible with the electronic monitoring sensor (compatible ICS and ICS or LABA medications include Flovent [fluticasone], QVAR [budesonide], Advair MDI [fluticasone-salmeterol], Dulera [mometasone-formoterol], and Asmanex [mometasone-furoate]); (3) children and families must live or receive primary care in Philadelphia ZIP codes with the highest child asthma morbidity (greater than 100 pediatric asthma hospitalizations per year, according to Pennsylvania Health Care Cost Containment Council [22] hospitalization data); and (4) the parent or legal guardian must have a mobile phone plan with unlimited text messages.

Children will be excluded from the study if they are prescribed a controller inhaler to which the electronic device cannot affix (eg, any dry powder inhaler, Symbicort [budesonide or formoterol], or Seretide [fluticasone-salmeterol]) as their primary controller medication. Children with comorbid conditions that may influence the treatment of asthma (such as chronic lung disease, structural heart disease, or cystic fibrosis) will be excluded. Families will be excluded from the study if they have active state social services involvement or if they are non-English speaking. Subjects with significant developmental delays will also be ineligible.

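### Prescription changes are noted only if a caregiver mentions them, as a reason for missing data; a dated question at both follow-up calls would protect the adherence denominator, mainly for the exploratory trajectories

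*Protocol article*

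**What the plan says.** All references are to the protocol article.

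- **Capture of changes.** Data Analysis, Feasibility, lists examples of why actuation data may be missing and ends: "or prescription changes) will be recorded if described by the caregiver during follow up or syncing issue calls described above".
- **Call 1.** Under Intervention Phase: "All participants will be asked whether they have run out of ICS medication and if they had any problems using the electronic sensor". The same paragraph says that problems that could lead to missing data are recorded, and that families are reminded to move the sensor to a refilled inhaler.
- **Call 2.** Under Follow-up Phase: "Participants will be asked again whether they have run out of ICS medication or if they had any problems using the electronic sensor".
- **Other contacts.** Outcome Measures, Feasibility, adds "individual calls for participants whose sensors fail to sync within the first 2 days of the intervention phase". Under Propeller Health System, staff can see when a sensor last synced, but the research app is limited: "it does not display data on device actuations". Staff stay blind to use until the intervention interval ends.
- **Regimen.** Eligibility concerns the inhaler at discharge: "the ICS prescribed on discharge must be an MDI compatible with the electronic monitoring sensor". After that: "Participants will be instructed to use the inhaler as directed by their physician".
- **Measure.** Outcome Measures, Limited Efficacy, defines the outcome over the 30-day intervention phase as "average percent adherence (observed actuations or prescribed actuations"; I read this as observed over prescribed. The trajectory models use daily adherence from both the intervention and follow-up phases.

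**The concern.** A prescription change need not cause missing data. If the dose is halved or doubled in puffs, the sensor goes on transmitting. If the inhaler is stopped or set aside for another, its sensor can still sync and report no actuations. In each case the data look complete, so a procedure that collects reasons for missing data may not reach the case. A caregiver asked only about running out and about sensor trouble has no particular prompt to mention a visit at which the controller was changed.

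If nothing else records the change, observed puffs are divided by a prescribed count that no longer applies. The score is too low after a reduction or stop and too high after an increase. A family following its physician's advice could then appear non-adherent. This matters most for the trajectories, because the Discussion wants them to show how, when and why ICS use falls away after an exacerbation, and a clinician-directed stop can look like such a fall. Dates that nobody asks for may not be recoverable at analysis.

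**Working it through.** The article gives no figure for this, so there is none to reproduce. The check sizes one unrecorded change.

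**Inputs from the article.** 40 children at 1:1, so about 20 per arm; a 30-day efficacy window; monitoring to day 60; adherence of 11-37% in urban minority populations (Introduction).

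**Assumptions.** One lasting change after day *d* (base case 15); *r* = new over old prescribed puffs (0 for a stop, 0.5 halved, 2 doubled); adherence *a* to the regimen in force stays constant; no source records the change.

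**Formulas.**
- Average daily score after the change = *r* × *a*
- Child's 30-day score = *a* × [*d* + *r*(30 − *d*)] / 30
- Shift in arm mean per affected child = *a* × (*r* − 1) × (30 − *d*) / 30 / 20

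**Base case, *d* = 15** (each cell: true 11% / true 37%):

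| Change | Average daily score afterwards | Child's 30-day score | Arm-mean shift, points |
|---|---|---|---|
| Stop | 0% / 0% | 5.5% / 18.5% | −0.275 / −0.925 |
| Halved | 5.5% / 18.5% | 8.25% / 27.75% | −0.14 / −0.46 |
| Doubled | 22% / 74% | 16.5% / 55.5% | +0.275 / +0.925 |

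**Sensitivity.** For a stop at *a* = 37%, day 10 gives 0.37 × 20/30 / 20 = −1.23 points, day 20 gives −0.62 and day 25 gives −0.31. At *a* = 50%, the childhood average quoted in the Introduction, a stop at day 15 gives 0.50 × 15/30 / 20 = −1.25 points.

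**Where the mis-scored days fall.** A lasting change after day *d* < 30 affects 30 − *d* days of the efficacy window and 60 − *d* days overall, so 30 / (60 − *d*) of them lie after day 30:

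| Day of change | Days affected to day 30 | Days affected to day 60 | Share after day 30 |
|---|---|---|---|
| 7 | 23 | 53 | 57% |
| 15 | 15 | 45 | 67% |
| 21 | 9 | 39 | 77% |
| 30 | 0 | 30 | 100% |

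The share is never below half. With change days uniform over 60 days, the means are 7.5 affected days in the efficacy window and 30 overall, so 75% fall after day 30. The day counts are upper limits, because the follow-up phase starts only when call 1 is completed and lasts up to 30 days.

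**How much of a stop is artefact.** After a stop at day 15, 45 days would read zero if they were scored. Many of those doses would have been missed anyway: the excess is 45 × 0.11 = 4.95 to 45 × 0.37 = 16.65 days' worth of doses.

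**The case against.** The strongest reply is that the article is a condensed account. It does not give the source of the prescribed count, the survey items or the call scripts, and chart review may supply regimen dates. That stands, and it makes the consequence conditional. It does not remove the point, because the article does state a capture method for prescription changes, and that method is passive.

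A reader might infer more than the text supports:

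- **That the denominator is fixed at discharge and stopped days count as zero.** Neither is stated. Prescribed actuations could mean the regimen in force, and listing prescription changes among reasons for missing data suggests that days after a reported stop might be set to missing. The exposure is to changes that nobody reports.
- **That the calls collect nothing relevant.** They do collect reasons for missing data and problems that may cause it. What is not described is a question on clinician-directed changes.
- **That blinding to actuations prevents detection throughout.** It ends with the intervention interval, and both calls come after that. It explains only why stopped use on a syncing sensor prompts no enquiry during the first 30 days.
- **That every step-up or step-down distorts the score.** A change of strength at the same number of puffs causes no error.
- **That the trajectory groups, or the comparison between arms, are shown to be biased.** The models use daily values, and no effect on group membership has been worked out. No difference in regimen changes between arms is shown, and similar numbers in both arms would largely cancel.

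It is also fair to say that the primary outcomes are feasibility outcomes, and that the Limitations section disclaims power for adherence and for trajectories.

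**Conclusion.** The point holds as a cheap improvement of minor weight. The article anticipates prescription changes, but its described method records them only if volunteered and only as an explanation for missing data. A change in puffs, a stop or a switch on a syncing sensor may therefore go undated and be scored against an outdated count.

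In the base case the 30-day arm mean moves by less than 1 point per affected child; an earlier change or higher adherence takes it somewhat above 1 point. At least half of the mis-scored days fall after day 30, so the exploratory trajectories carry most of the exposure, though an early change touches the 30-day outcome too.

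This rests on an assumed day and type of change, constant adherence to the regimen in force, and no capture in any source not shown. The number of affected children is unknown, so no total effect can be given.

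**What to change.** 1. At both follow-up calls, ask every caregiver whether a clinician has changed, stopped or replaced the controller inhaler, on what date, and what the new daily puff count is.
2. Compute prescribed actuations from the regimen in force on each day.
3. Treat days after a reported stop or a switch to an incompatible inhaler as not evaluable, both in percent adherence and in the trajectory input.

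The cost is one dated question on two calls already planned and one regimen field in the analysis data. The drawback is reliance on dates that caregivers recall.
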